### Phase 7: Systems modelling

We will also draw on the unique capacity of simulation as a systems analysis tool. Systems analysis tools are used by engineers to understand how complex systems operate, how well these systems meet operational goals, and how they can be improved [6]. They can be (and have been) used in healthcare to address a number of challenges, including ED crowding [6], but commonly have not included consideration of the pre-hospital emergency medical service [6]. EDs do not exist in isolation, but are part of a complex health system and as such policy must be based on an understanding of how they relate to pre-hospital circumstances, to the rest of the hospital and to care in the surrounding community [26], p529. Our simulation study will enable a more multi-factorial ‘system-wide’ approach to addressing ED crowding, whilst at the same time specifically enabling modelling of the impact of the introduction of ECPs on ED demand.

Using an ecological systems approach, we will model the potential impact of ECPs on ambulance service utilisation and metropolitan ED demand [27]. A whole of system approach is required to understand the complex interplay among these factors and sophisticated systems simulation can help understand the impacts of possible policy interventions and individual responses, through the running of virtual ‘what if’ experiments.

#### Statistical analysis

a) The characteristics of each of the two groups (i.e. paramedic identified potential ECP candidate patients versus non-ECP patients) will be described using percentages for categorical variables; mean ± standard deviation and median with interquartile range for continuous variables.

b) Comparisons between the two groups (i.e. ECP candidate patients versus non-ECP patients) will be performed using chi-square tests for categorical variables; and Mann-Whitney ‘U’ (non-parametric) or t-test (parametric) for continuous variables, depending on the distribution of the data. Significance will be set at p<0.05.

c) Multivariable logistic regression models will be used to (i) estimate the odds of a patient being identified by the paramedics as an ECP candidate based on their demographic and clinical condition; and (ii) model the ED disposition (admit/not admit) based on the ECP candidate status identified by the paramedics, adjusted for potential confounding characteristics of the patient and/or condition. Covariates will be included on the basis of clinical plausibility and univariate associations. Models will be run with the inclusion of all covariates deemed relevant, i.e. not using any ‘step-wise procedure’. A-priori defined interaction terms will be tested and included in the models if significant.

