### Phase 1: Collect baseline data

Over a 3 month period, we will include all patients within the Perth metropolitan area attended by SJA-WA paramedics and transported to one of the11 Perth EDs. The paramedics will routinely indicate on the e-PCR whether, in their opinion, they consider that the patient they attended could have *potentially* been managed by an ‘extended care paramedic’ through either a) ‘see and treat’ , or b) ‘see and refer’ strategies. (All paramedics will be emailed a clinical circular outlining the process for indicating on the e-PCR the possible alternative pathways.) In addition, the details of any patients attended by SJA-WA paramedics but not transported to ED (currently recorded as ‘Ambulance Not Required’ - ANR) will also be captured as part of the study.

The ED disposition and other clinical outcomes of the patients in this study cohort will be obtained via the WA EDIS data, WA hospital data and WA death registry data. Further clinical information about diagnostic tests performed and the principal reason for the patient’s admission to hospital or discharge from the ED will be abstracted from medical record reviews for a sample of patients.

The characteristics of the patients identified as potential candidates for non-transport to ED will be compared to those who were flagged as requiring transport to ED, with respect to:

a. Age, gender, socioeconomic status (based on residential address), geographical location, residential care facility, pre-hospital clinical problem code, ambulance dispatch priority code, time of day, day of week (SJA-WA data).

b. The Australasian Triage Score (ATS) [25] and presenting complaint recorded in ED.

c. ED diagnosis; ED disposition (discharge home; admit; died) and time in ED.

d. For those admitted to hospital: diagnosis, length of stay, procedures, disposition.

e. For all patients: representation at ED (or ambulance attendance) within 24 hours; 48 hours and within one week of the initial ambulance attendance.

f. A random sample of patients identified as being able to be managed in the community (proportionately across each hospital and major diagnosis category) will have medical record review by the study research nurse, to determine the nature of the clinical care received.

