### Phase 2: Development of ‘trial’ ECP clinical protocols

A clinical reference group will be established with study investigators and clinical/community stakeholders (including paramedics). Based on the findings gained from Phase 1 of the study together with the best available evidence, clinical protocols for patients who could either be a) seen and treated on scene by a paramedic or b) referred to another community service will be developed. This phase of the study will involve an iterative process of refinement (through face-to-face meetings and document review) of the clinical protocols for the appropriate identification and management of patients under the extended scope of paramedic practice model of care (ECPs).

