### Phase 3: Test the ECP protocols (simulation)

Following the development of clinical protocols for ECPs in Perth, a second 3-month cohort of SJA-WA patients will be studied. For this cohort, paramedics will routinely identify (on the e-PCR) whether the patient that they attended met the defined clinical protocol criteria for management by an ECP through either a) ‘see and treat’, or b) ‘see and refer’ strategies. Patient outcomes will be followed up, as described for Phase 1 of the study, to again compare the demographic, clinical characteristics, ED disposition and re-presentation at ED or readmission to hospital.

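### The stated analysis pools see-and-treat with see-and-refer patients in one ECP-candidate group and specifies no outcome results by pathway

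*Protocol article*

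**What the plan says.** The protocol article keeps two routes apart from data capture through to protocol development.

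- **Phase 1.** Paramedics indicate whether a patient might have been handled by see and treat (a) or see and refer (b). The instructions refer to pathways in the plural: "All paramedics will be emailed a clinical circular outlining the process for indicating on the e-PCR the possible alternative pathways".
- **Phase 2.** The reference group develops "clinical protocols for patients who could either be a) seen and treated on scene by a paramedic or b) referred to another community service".
- **Phase 3.** Paramedics record "whether the patient that they attended met the defined clinical protocol criteria for management by an ECP through either a". The alternative is route b, and the lettering is the same as in Phase 1.

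The comparisons use one combined group.

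- **Phase 1.** "The characteristics of the patients identified as potential candidates for non-transport to ED will be compared to those who were flagged as requiring transport to" the ED.
- **Phase 3.** "Patient outcomes will be followed up, as described for Phase 1 of the study". No split by route is named.
- **Statistical analysis, item a.** "The characteristics of each of the two groups (i.e. paramedic identified potential ECP candidate patients versus non-ECP patients", with descriptive summaries for each.
- **Item b.** The tests compare the same two groups.
- **Item c.** Model (i) has candidate status, yes or no, as its outcome. Model (ii) has it as the exposure for admission.

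Phase 4 then asks the reference group to judge safety and appropriateness from the Phase 3 data and to refine the protocols.

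**The concern.** The Background puts patient safety ahead of the effect on ED demand, and Phase 4 has to turn the Phase 3 results into revised criteria. Patients thought suitable for treatment on scene and patients thought suitable for referral may well have different conditions. If so, their admission, re-presentation and death rates may differ too. A pooled rate is a weighted average that leans towards the larger route. It can look acceptable while the smaller route does badly, or look poor when only one route is at fault. In either case the reference group would not learn from the stated analysis which set of criteria to tighten.

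**Working it through.** **1. Is the pooling stated, or only left unsaid?** Item a names two groups and says which two they are. Item b repeats them, and model c(ii) uses one candidate status. The grouping is therefore a stated choice. Item c also mentions pre-defined interaction terms without listing them. Pathway exists only among flagged patients, so an ordinary interaction with candidate status would not recover it.

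**2. How far can pooling mislead?** The article gives no flagged share, pathway mix or outcome rate, so there is no plan figure to reproduce. All rates and mixes below are assumptions.

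Let w be the see-and-treat share of flagged patients, and T and R the admission rates for see and treat and see and refer.

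Pooled rate = w × T + (1 − w) × R. If R is the worse rate, the pooled figure falls short of it by w × (R − T).

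| w | T | R | Pooled rate | Shortfall against the worse pathway |
|---|---|---|---|---|
| 0.7 | 5% | 20% | 3.5 + 6.0 = 9.5% | 10.5 points |
| 0.7 | 5% | 30% | 3.5 + 9.0 = 12.5% | 17.5 points |
| 0.5 | 5% | 20% | 2.5 + 10.0 = 12.5% | 7.5 points |
| 0.3 | 5% | 20% | 1.5 + 14.0 = 15.5% | 4.5 points |
| 0.2 | 20% | 8% | 4.0 + 6.4 = 10.4% | 9.6 points (see and treat worse) |

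The masking can run in either direction. It is zero if the two rates are equal.

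**3. Are there enough patients to report by pathway?** The Background gives 105,327 transports to ED among 132,862 attended cases in 2012. The ratio is 105,327 / 132,862 = 79.3%, which agrees with the article. Spread evenly over the year, a 3-month cohort has 105,327 / 4 ≈ 26,332 transports.

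- Assume 5% to 20% are flagged: 1,317 to 5,266 patients.
- Assume the smaller pathway is 30% of these: 395 to 1,580 patients.
- 95% half-width = 1.96 × √(p(1 − p)/n). At p = 5% this is 2.1 points (n = 395) to 1.1 points (n = 1,580). At p = 20% it is 3.9 to 2.0 points.

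On these assumptions, each pathway could be reported with useful precision from one cohort.

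**The case against.** The strongest reply is that the study asks one question of both routes: could this patient have stayed out of the ED? A candidate versus non-candidate contrast matches that question and is a legitimate main comparison. This stands, and the two-group contrast should stay. Making three groups primary and demoting the pooled one would be a preference, not a correction.

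Four further replies limit the point.

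- **A reader might infer that neither pathway's safety is tested.** The text does not support that. Disposition, re-presentation and deaths are obtained for the whole cohort, and nothing in Phase 4 stops the group from splitting the Phase 3 data by route.
- **A reader might infer that each route has its own protocol.** Phase 2 speaks of protocols for patients in either route. The Abstract refers to a protocol in the singular, and Phase 4 to a single alternative pathway.
- **It is tempting to argue that see-and-treat patients are at more risk because nobody else may see them.** That does not fit this design. Practice is unchanged and the flagged patients whose ED outcomes are studied still went to the ED, so the label brings no difference in aftercare. Only case mix could make the observed rates differ.
- **The document is a condensed article, and a fuller plan may add a breakdown.** That is possible and lowers the weight of the point. It does not remove it, because the article states the grouping explicitly.

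**Conclusion.** The point holds in a limited form. The article distinguishes two routes at data capture and in protocol development, then pools them in every stated comparison and model and specifies no outcome analysis by pathway. A pooled rate could therefore mask a worse rate in one route, and it gives Phase 4 no direction on which criteria to refine.

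The size of any masking cannot be known from the document. The shortfalls of 4.5 to 17.5 points in the working rest wholly on assumed rates and mixes, and even their direction is open. The conclusion rests on two assumptions: that case mix may differ between the routes, and that the e-PCR entry stores which route was chosen, as the Phase 1 instruction indicates. It is not a finding that safety goes unassessed.

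**What to change.** Keep the two-group contrast in items a to c and add the following to the Statistical analysis section:

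1. Report ED disposition, re-presentation at 24 hours, 48 hours and 7 days, and death separately for see-and-treat and see-and-refer patients, with 95% confidence intervals, at least for Phase 3.
2. Fit model c(ii) a second time with candidate status at three levels: see and treat, see and refer, and non-ECP.
3. State under Phase 4 that the reference group receives these results when it reviews the protocols.

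The cost is some analysis wording and wider intervals for the smaller pathway. No new data are needed if the e-PCR stores the route chosen, which should be confirmed before Phase 3 starts.

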### Ambulance services in WA

All road-based emergency ambulance services in WA are provided by a single ambulance service provider, St John Ambulance (Western Australia) [21]. Emergency phone calls (‘000’) for an ambulance are received by the ambulance service operations centre and computer-aided dispatch (CAD) used to assign calls to ambulance paramedic crews. During the study period, patient care data will be recorded by the paramedics using the existing electronic patient care record (e-PCR). The e-PCR data are linked to the CAD data for each episode of care.

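### The named group tests and regressions make no stated allowance for clustering by paramedic or repeat patient, so p-values can be too small for characteristics that also cluster

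*Protocol article*

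**What the plan says.** In the Protocol article, Statistical analysis, item b, group comparisons "will be performed using chi-square tests for categorical variables", with "Mann-Whitney ‘U’ (non-parametric) or t-test (parametric) for continuous variables, depending on the distribution of the data". The threshold follows: "Significance will be set at p<0.05". In item c, model (i) is to "estimate the odds of a patient being identified by the paramedics as an ECP candidate", and model (ii) is to "model the ED disposition (admit/not admit) based on the ECP candidate status identified by the paramedics". Covariates enter on clinical plausibility and univariate association, and pre-specified interactions stay in the model when they reach significance. No item mentions correlation within paramedic, crew or patient.

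Other sections show how the data arise:

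- Under Ambulance services in WA, computer-aided dispatch is "used to assign calls to ambulance paramedic crews", and the records are linked episode by episode.
- Under Phase 1, "we will include all patients within the Perth metropolitan area attended by SJA-WA paramedics" and transported to a Perth ED over 3 months. The flag records the attending paramedic's opinion, after an emailed circular. Item e of the Phase 1 comparison list counts repeat ED presentation or ambulance attendance within 24 hours, 48 hours and one week.
- Under Phase 3, the paramedic still records the flag, now against defined protocol criteria.

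**The concern.** The variable that defines the two groups, which is also the outcome of model (i), is a rating by many raters. Paramedics can be expected to differ in how readily they flag, most of all in Phase 1, where no criteria are set. Patients who call more than once add a second source of dependence, and nothing in the article restricts the analysis to one attendance per patient.

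Several characteristics in the Phase 1 list could follow the crew, depot or shift: geographical location, area-based socioeconomic status, time of day and day of week. Others, such as gender, stay fixed across a patient's attendances. For these, a test that assumes independence can report an association that partly reflects who attended or who called again.

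The item b results matter beyond description. Univariate associations help choose the covariates for item c, significance decides which interactions stay, and the Phase 1 findings go to the group that drafts the ECP protocols.

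**Working it through.** The article gives no sample size, ICC, number of paramedics or repeat-attendance rate, so there is no design figure to reproduce. The one stated percentage checks: 105,327/132,862 = 79.3%.

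**Volume (Background, 2012 figures).** 105,327/4 = 26,332 transports per 3 months. The number of paramedics is an assumption: 300, 500 or 1,000 gives m = 87.8, 52.7 or 26.3 attendances each.

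**Formula.** The flag and the compared characteristic both vary within a paramedic, so the variance inflation for their association is approximately

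DEFF = 1 + (m − 1) × ICC(flag) × ICC(characteristic),

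and the true size of a nominal two-sided 5% test is 2 × [1 − Φ(1.96/√DEFF)]. The article does not state sidedness; two-sided is assumed.

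**Results.** All ICCs are assumptions. Column heads give ICC(flag) / ICC(characteristic).

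| Paramedics | m | 0.05 / 0.01 | 0.10 / 0.01 | 0.10 / 0.05 | 0.20 / 0.10 |
|---|---|---|---|---|---|
| 300 | 87.8 | 5.5% | 6.0% | 10.2% | 23.6% |
| 500 | 52.7 | 5.3% | 5.6% | 8.1% | 16.9% |
| 1,000 | 26.3 | 5.1% | 5.3% | 6.5% | 11.0% |

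Worked example, top right: DEFF = 1 + 86.8 × 0.20 × 0.10 = 2.74 and √DEFF = 1.654, so the size is 2 × [1 − Φ(1.96/1.654)] = 0.236. If the characteristic has an ICC of zero, DEFF = 1 and the size stays at 5% whatever the flag ICC.

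**Simulation check.** The chi-square test was simulated with beta-binomial clusters: 500 paramedics with 53 attendances each, 4,000 replicates, mean flag rate 15% and mean characteristic prevalence 40% (both assumed). Rejection rates were 0.051 (ICCs 0.10 and 0), 0.058 (0.10 and 0.01), 0.083 (0.10 and 0.05), 0.118 (0.20 and 0.05) and 0.172 (0.20 and 0.10). These agree with the formula.

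**Repeat patients.** With an assumed weighted mean of 1.1 to 2.0 attendances per patient and an ICC product of 0.1 to 0.5, DEFF runs from 1 + 0.1 × 0.1 = 1.01 to 1 + 1.0 × 0.5 = 1.50, and the true size from 5.1% to 11%. For a trait fixed within patient, ICC(characteristic) = 1, so the product is simply the flag's ICC within patient.

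**Which results are exposed.** In the worst case above, a naive z must exceed 1.96 × 1.654 = 3.24 (p about 0.001) to be significant at a true 5%. With some 26,000 attendances, strong associations will pass that mark. Those with naive p-values between about 0.001 and 0.05 may not.

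**The case against.** The strongest objection is that this is a condensed article and that its analysis plan, if there is one, is not shown. Variance estimation and the handling of repeat attendances are often left to that plan. For item c this largely stands: a mixed or robust model would be consistent with naming only logistic regression. It does not dispose of item b, which fixes specific tests, so allowing for clustering would mean changing them.

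It is also fair that no p-value alone decides what reaches the protocol group. That group weighs other evidence, covariates also enter on clinical plausibility without stepwise selection, and the protocols are tested in a second 3-month cohort. This limits the harm but does not make the tests valid.

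Four stronger readings are tempting, and the documents do not support them:

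- A reader might apply the usual design effect, 1 + (m − 1) × ICC, and conclude that error rates are far higher. That formula fits a factor constant within paramedic, and the Phase 1 list contains none.
- A reader might add a design effect for hospitals. All 11 Perth EDs are included, so for this population they are fixed strata, not a sample of clusters.
- A reader might say that confidence intervals will be too narrow. The Statistical analysis section plans none.
- A reader might say that re-presentations are counted twice. Item e counts from an initial attendance, and the article does not say whether a repeat transport also becomes a new index case. Double counting is possible but not stated.

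**Conclusion.** The point holds in a limited form. The item b tests assume independence that the described data collection does not provide, and no allowance is stated for the item c models. P-values can be too small, but only where the compared characteristic also clusters by paramedic or patient. Under the assumed workforce and ICCs, the true size of a nominal 5% test is about 5% to 24%, with essentially no inflation for characteristics that do not cluster. The document supplies only the volume, so the size within that range is unknown. Strong associations are safe; weak associations, univariate covariate choice and interactions retained on significance are exposed. This is worth correcting before analysis but does not undermine the design.

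**What to change.** - State the attendance (episode of care) as the unit of analysis.
- Replace the simple group tests with versions that allow for clustering by paramedic or crew and by patient.
- Fit models (i) and (ii) with GEE, a mixed model or cluster-robust variance. Paramedic and patient are crossed rather than nested, so two-way cluster-robust variance is one simple option. A random intercept is not required, and it would change the odds ratio from a marginal to a cluster-conditional one.
- Enter hospital as a fixed effect in model (ii).
- For item e, define the index attendance so that a re-presentation is not also counted as a new index case. Add a sensitivity analysis on the first attendance per patient.

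The cost is modest programming and somewhat larger p-values. Crew and patient identifiers must be kept in the linked data; the article describes the record linkage but does not confirm that these identifiers will be available for analysis.

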**Methods/Design:**

St John Ambulance Western Australia paramedics will indicate on the electronic patient care record (e-PCR) of patients attended in the Perth metropolitan area if they consider them to be suitable to be managed in the community. ‘Follow-up’ will examine these patients using ED data to determine the patient’s disposition from the ED. A clinical panel will then develop a protocol to identify those patients who can be safely managed in the community. Paramedics will then assess patients against the derived ECP protocols and identify those deemed suitable to ‘see and treat’ or ‘see and refer’. The ED disposition (and other clinical outcomes) of these ‘ECP protocol identified’ patients will enable us to assess whether it would have been appropriate to manage these patients in the community. We will also ‘track’ re-presentations to EDs within seven days of the initial presentation. This is a ‘virtual experiment’ with no direct involvement of patients or changes in clinical practice. A systems modelling approach will be used to assess the likely impact on ED crowding.

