ECPs provide alternative care pathways for patients who call for an ambulance and meet certain pre-defined criteria, such as the patient having a minor illness or injury, or only requiring basic medical advice or reassurance [15]. Through a ‘see and treat’ or a ‘see and refer’ strategy it is suggested that they can assist in reducing ambulance transport to hospital [16]. Whilst there is clear enthusiasm about the concept of ECPs as an alternative community-based model of emergency/primary health care, there is no good quality research data in Australia to support the efficacy, safety or cost-effectiveness of an ECP programme. It needs to be established that patients seen by ECPs do not end up presenting to ED within hours/days of the initial ECP attendance – possibly in a worse clinical condition than their initial presentation – or come to harm or die because of an unrecognised life-threatening condition.

Our project will develop and test (through simulation) the feasibility and safety of empirically derived clinical protocols for an extended care paramedic (ECP) role for the Perth metropolitan area. We are aware of the fact that paramedics do not have the same repertoire of clinical assessment skills as emergency physicians, nor do they have access to the same array of diagnostic tests. Of concern to all clinicians is the risk of failing to identify potentially catastrophic events, such as sepsis, stroke or myocardial infarction. Thus, while we are interested in modelling the impact of the introduction of ECPs on ED demand and ED crowding, our primary concern will be patient safety.

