### Ethics approval

No direct involvement of patients is required and there will be no change in actual clinical practice in this study. Human Research Ethics Approval has been obtained from the University of Western Australia (#RA/4/1/5514), with waiver of informed consent. We also have human research ethics approval to follow-up a sample of patients at three tertiary teaching hospitals in Perth: Sir Charles Gairdner Hospital, Royal Perth Hospital, Fremantle Hospital, and the private hospital St John of God - Murdoch. This may be extended to include other hospitals depending on the findings from the initial phase of the study.

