### Phase 4: Refinement of the ECP protocols

The clinical reference group will be reconvened to review the data from Phase 3 to determine the safety and appropriateness of the alternative paramedic pathway for the management of patients flagged as suitable for non-transport to ED and to refine the clinical protocols as required.

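### The between-group tests and the adjusted admission model do not measure how often the paramedic's flag is wrong, which is the study's safety question.

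*Protocol article*

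**What the plan says.** **Aim.** The Background of the Protocol article states that "our primary concern will be patient safety". The Abstract (Methods/Design) says that the ED disposition and other clinical outcomes of protocol-identified patients "will enable us to assess whether it would have been appropriate to manage these patients in the community". In Phase 4 a clinical reference group reviews the Phase 3 data to "determine the safety and appropriateness of the alternative paramedic pathway for the management of patients flagged as suitable for non-transport to ED". Under Ethics approval, "there will be no change in actual clinical practice in this study".

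**Analysis.** The Statistical analysis section has three items:
- Item a describes candidates and non-candidates with percentages, means and medians.
- Item b compares the two groups by chi-square, Mann-Whitney or t-test. "Significance will be set at p<0.05".
- Item c has two logistic models. Model c(i) predicts the flag from demographic and clinical condition. Model c(ii) has admit/not admit as outcome and the flag as predictor, "adjusted for potential confounding characteristics of the patient and/or condition". On covariate choice: "Covariates will be included on the basis of clinical plausibility and univariate associations".

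**Pathways.** Phases 1 to 3 separate see-and-treat from see-and-refer, in the flagging and in the protocols to be written. The Statistical analysis section names only two groups, candidates and non-candidates.

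**The concern.** The aim sets an absolute question inside the flagged group: of the patients a paramedic would have kept out of the ED, how many turned out to need admission, died or came back, and how precisely is that known? The inferential analyses answer different questions.

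Item b asks whether flagged and unflagged patients differ. They should differ, and at this cohort size even a trivial difference will be significant.

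Model c(ii) treats the flag as an exposure whose association with admission must be freed of confounding. But nobody's care depends on the flag. Age, presenting problem and dispatch priority are information that a paramedic, or a written protocol, uses to decide. Adjusting for them asks whether the flag carries information beyond them, which is a different matter from whether it sorts patients safely.

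At stake is the evidence that reaches the reference group. A sound flag could come with an unimpressive adjusted odds ratio, and a poor one with an impressive odds ratio. With the pathways pooled, an acceptable overall figure could also hide a poor one in either pathway.

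**Working it through.** **Inputs.** The article gives no sample size, power, event count or accuracy target, so there is no design figure to reproduce. The Background figure used for scale checks: 105,327 / 132,862 = 79.28%, stated as 79.3%. Assuming an even spread over the year, a 3-month cohort has 105,327 / 4 ≈ 26,332 transported patients. Flag rates, admission rates and odds ratios (OR) are not in the article; all those below are assumptions.

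**1. Significance comes easily at this size (item b).** The smallest observed difference with p<0.05 is about 1.96 × √[p(1−p)(1/n1 + 1/n0)]. With 20% flagged, n1 = 5,266 and n0 = 21,065:
- p = 0.5 gives 0.0151, or 1.5 percentage points
- p = 0.1 gives 0.0091, or 0.9 points

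With 15% flagged (n1 = 3,950), true admission rates of 37% and 40% would be told apart with 95% power, although a flag wrong in 37% of cases is of little use.

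**2. One odds ratio fits very different error rates.** Fix the OR at 0.40, with 15% flagged. If a fraction p0 of unflagged patients is admitted and o0 = p0/(1−p0), the flagged rate is 0.40·o0/(1 + 0.40·o0).

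| Unflagged admitted | Flagged admitted | 95% CI (Wilson, n = 3,950) | Chi-square p |
|---|---|---|---|
| 10% | 4.3% | 3.7–4.9% | 7.0e-31 |
| 30% | 14.6% | 13.6–15.8% | 4.1e-88 |
| 50% | 28.6% | 27.2–30.0% | 1.5e-136 |

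Every test is overwhelmingly significant, while the share wrongly flagged varies more than sixfold (28.6 / 4.3 = 6.7).

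**3. Adjustment can mislead in both directions (item c(ii)).** Take three severity strata holding 40%, 40% and 20% of patients. For simplicity, everyone not admitted counts as discharged.

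*Good flag.* Admission is 3%, 40% and 85% by stratum, whatever the flag; 40%, 1% and 0.05% are flagged.
- Flagged: 0.16 + 0.004 + 0.0001 = 0.1641
- Flagged and admitted: 0.16×0.03 + 0.004×0.40 + 0.0001×0.85 = 0.006485, so 0.006485 / 0.1641 = 4.0%
- Unflagged and admitted: 0.24×0.03 + 0.396×0.40 + 0.1999×0.85 = 0.335515, so 0.335515 / 0.8359 = 40.1%
- Crude OR 0.06; severity-adjusted OR 1.00 (95% CI 0.82–1.22)
- Share of discharged patients flagged: 0.157615 / 0.658 = 24%. Share of admitted patients not flagged: 0.335515 / 0.342 = 98%

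*Poor flag.* Admission in unflagged patients is 10%, 45% and 85%; the OR is 0.40 within each stratum, so flagged patients have 4.3%, 24.7% and 69.4%. Sicker patients are flagged more often: 5%, 20% and 25%.
- Flagged: 0.02 + 0.08 + 0.05 = 0.15
- Flagged and admitted: 0.02×0.0426 + 0.08×0.2466 + 0.05×0.6939 = 0.0553, so 0.0553 / 0.15 = 36.8% (before rounding)
- Unflagged and admitted: 0.38×0.10 + 0.32×0.45 + 0.15×0.85 = 0.3095, so 0.3095 / 0.85 = 36.4%
- Crude OR 1.02; adjusted OR 0.40 (95% CI 0.37–0.44), p about 8e-99
- Share of discharged patients flagged: 0.0947 / 0.6352 = 14.9%. Share of admitted patients not flagged: 0.3095 / 0.3648 = 84.8%. Flagging 15% at random would give 15% and 85%

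The adjusted ORs are from logistic regression on the expected counts for 26,332 patients. The unadjusted proportions and the two accuracy measures rank these flags correctly; the adjusted OR reverses them.

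**The case against.** The strongest reply is that the needed quantity is already there. Item a gives percentages, and the Phase 1 lists include ED disposition (discharge, admission, death) and re-presentation at 24 hours, 48 hours and one week. Phase 4 leaves the judgement to clinicians, who would see those percentages, helped by medical record review of a sample. Intervals and accuracy indices are often left to a fuller document. Whether paramedic opinion adds to recorded characteristics is also a fair secondary question before written protocols are drawn up.

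Much of this stands, and it rules out several stronger readings that a reader might infer:
- *That the plan yields no safety data.* It does, descriptively.
- *That a protocol would be approved because p<0.05 or because of the adjusted OR.* The article says neither; the reference group decides.
- *That all of item c treats the flag as an exposure.* In c(i) the flag is the outcome, and that model is a reasonable description of flagging behaviour.
- *That ED triage score and ED diagnosis will enter the models.* The Phase 1 lists name variables for comparison. The Statistical analysis wording does not exclude ED-derived covariates, but it does not say they will be used.
- *That the adjusted OR will in fact be near 1.* In the good-flag example this is built in, because admission depends only on the severity that is adjusted for. It shows what can happen, not what is likely in Perth.

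The reply does not rescue b and c(ii) as safety analyses. The point does not turn on an omitted detail: the article itself fixes the tests, the adjusted model and the confounding rationale, and these do not fit its stated aim.

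**Conclusion.** The point holds for items b and c(ii). Neither estimates the share of flagged patients for whom the flag was wrong, no inferential analysis targets that share, and the analysis section pools two pathways that the rest of the study keeps apart.

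The conceptual part rests only on the article: the flag is a classification, care is unchanged, and the decision concerns flagged patients. The size is illustrative. Under the assumed rates, one OR of 0.40 is compatible with 4.3% to 28.6% of flagged patients being admitted, and the adjusted OR can be 1.00 for a good flag and 0.40 for a worthless one. How far crude and adjusted results would part in the real data depends on flag rates, admission rates and how fully the recorded covariates capture severity, none of which the article gives.

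**What to change.** In the Statistical analysis section, for Phases 1 and 3:
- Make the main analysis the unadjusted proportion of flagged patients admitted from the ED, with its 95% CI, overall and separately for see-and-treat and see-and-refer.
- Report death and re-presentation within 7 days alongside, in the same breakdown.
- Add sensitivity and specificity of the flag against ED disposition, with admitted or died on one side and discharged on the other, so that a death in the ED is not counted as a correct flag.
- Keep c(i) as a description of flagging behaviour.
- Keep c(ii) as exploratory, with covariates known at the scene and fixed in advance, and drop the word confounding.

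The cost is wording: the data are those already planned and nothing changes for patients or paramedics. The adjusted OR is no longer a main inferential result, and estimates by pathway will have wider intervals than the pooled one. ED disposition is an imperfect standard for whether hospital was needed; the planned record review can help in interpreting it.
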